## Methods/design

### Aims

The main aim of this study will measure the effect of the implementation of a falls prevention programme based on temporal patterns and relative risks factors.

Secondary aims will be: (i) to identify temporal patterns in the incidence of hospital falls and intrinsic and external risks factors, pre- and post-intervention; (ii) to establish differences in temporal patterns according to the hospital setting (teaching or non-teaching) and the different types of wards (medical, surgical or mixed), pre- and post-intervention; (iii) to study the role of circadian time in drug administration for older people suffering from hospital falls, pre- and post-intervention; (iv) to identify the level of fatigue/sleepiness, attention and cognitive functionality of healthcare professionals intervening during hospital falls, pre- and post-intervention; and (v) to develop a uniform, simple and intuitive method to record hospital falls in order to improve the effectiveness of the registration of falls and to assess the implementation pre- and post-intervention.

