### Study variables

The main dependent variable will be the number of hospital falls. A hospital fall will be defined as “the consequence of a non-intentional and sudden movement towards the floor from a more elevated position” in hospital settings.

Other independent variables related with the patient who experiences a hospital fall include: (i) sociodemographic and economic data (age, gender, marital status and level of education); (ii) time (hour and minute, day and shift work) of fall; (iii) patient position (from the bed with or without bedrails, sitting, walking, and so on) and witness of the fall (roommate, family member, healthcare professional or no witness); (iv) use/no use of footwear and kind (open or closed); (v) cause of fall (instability (general instability and balance loss), dizziness (syncope, fainting and cardiovascular accident), drug adverse effects (diuretics, anti-hypertension and other drugs), accident (event with no identifiable cause), ambient-related (dropped objects, obstacles and wet floor), fragility (extreme fragility or weakness) or others); (vi) location of the fall (hospital room, bathroom, corridor, public area or others); (vii) fall-related injuries and severity (no wound/no consequences, minor wounds (grazes and minor contusions), afflicting wounds (contusions requiring stitches, fractures and skull trauma) or others (not afflicting wounds but still in need of minor medical intervention)); (viii) number and kind of coexisting clinical conditions; (ix) prescribed drugs and their time of administration; (x) chronotype measured by the Horne-Östberg Questionnaire (1976); (xi) quality of life in terms of body functionality, physical limitations, body pain, social role or function, mental health, emotional limitations, vitality, energy or fatigue and general perception about own health; and (xii) general health status in terms of somatic symptoms, anxiety, insomnia, social dysfunction and depressive symptoms.

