In the case of healthcare professionals, independent variables will be: (i) sociodemographic and economic data (age, gender, marital status, level of education, work experience and time worked in the unit); (ii) kind of contract and work unit; (iii) sleep pattern (quality and quantity of hours); (iv) chronotype measured by the Horne-Östberg Questionnaire (1976); (v) quality of life in terms of body functionality, physical limitations, body pain, social role or function, mental health, emotional limitations, vitality, energy or fatigue and general perception about own health; (vi) general health status in terms of somatic symptoms, anxiety, insomnia, social dysfunction and depression; and (vii) fatigue/sleepiness, attention and cognitive functionality.

Pre- and post-intervention will be:

***Step 1.*** Before implementing preventive measures: development of audits and seminars in order to improve, secure and control the registration of falls in hospitals and related factors, as well as others study variables (quality of life, functional status, chronotype, fatigue/sleepiness, attention and cognitive functionality). These interventions will be carried out by research nurses who are working in hospitals.

***Step 2.*** Implementation of a preventive measures programme: adjusted to the identification of temporal patterns of falls and relative risk factors of falls. As measures will be agreed with the managers of hospital centres, the interventions will be reflected in the official document of general objectives of the hospitals. Official document to which the personnel involved in the intervention have access. Preventive measures will be focused on organizational, educational and behavioural elements related to older people and healthcare professionals:

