After obtaining and analysing the falls that occurred during the first 18 months of the study, time-adjusted preventive measures will be carried out. These measures will be focused on organizational, educational and behavioural elements (previously mentioned).

The establishment of the programme of time-adjusted prevention measures will be carried out in May 2019 in the four centres. The post-intervention data collection will cover July 2019 to September 2020. The managers responsible for each centre, together with the research team, will implement the measures, and, as in the first phase, seminars will be held with healthcare professionals to focus on the recording of falls and their circumstances, as well as the variables included in the prevention programme.

During the post-intervention phase, the individual monthly audits will continue to be carried out with each Clinical Management Unit. This follow-up will make it possible to discern the effectiveness of the preventive measures.

***Phase 2***: For the retrospective study, the data will be delivered by the centres participating in the project to the Principal Investigator anonymized.

***Phase 3***: The development of the focus groups will be carried out in the facilities of the participating hospitals, ensuring the confidentiality of the participants. Four focus groups will be held at the Reina Sofia University Hospital in Córdoba and one in each of the three regional centres.

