Simple and multi-component Cosinor analyses will be used to explore temporal patterns [34]. This analysis uses the least squares method to approximate the time series of data to obtain one or more harmonics that fit the wavy shape that best explain the variance of the data set. The proportion of the overall variance (PR) represented by each harmonic component and the final multi-component curve function serve as goodness of fit parameters; the higher the PR is, the better representation by the total variance of the harmonic. The F-test statistic applied to the variance, represented by an approximation of the cosine curve versus a linear approximation of the time series data, was used to reject the null hypothesis of zero amplitude (absence of cyclical variation with respect to the period of time explored). The statistical significance of temporal patterns will be verified when the null hypothesis rejected for the F-test statistic is p < 0.5. The descriptive parameters of the statistically significant temporal patterns are the statistical estimated mean rhythm line (MESOR, the estimated rhythmic mean of the time series), amplitude (A, the numerical difference between the peak and valley values), temporal peak (φ, orthophase) and temporal valley (bathyphase); these last two variables are expressed according to the local midnight (00:00 h). The prominence of the temporal patterns, in terms of amplitude, will be expressed according to the MESOR as % AMP (greater prominence of the temporal variation, if the % AMP is greater). The variation will be low if % AMP < 25, moderate if 26–50, and high if > 50. To carry out the simple and multi-component Cosinor analyses, Chronolab software will be used [34].

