## Discussion

In a multi-causal adverse event such as a fall, a good initial evaluation of hospitalized elderly people and their registration is necessary. The results of the study, in addition to stimulating the epidemiological investigation of falls, are intended to prevent falls in the hospital setting. Obtaining temporal patterns in hospital falls allows establishing high-risk periods during the day. This fact may correspond to certain activities predictable in time. In this sense, previous studies applied in Italian hospitals have shown that the establishment of time-adjusted preventive measures has led to a decrease in the number of falls [20, 21]. All this will contribute to improvement in the safety of the individual, and as consequence of their health, environment (family environment) and social level (due to the decrease in costs that a decrease in dependency implies) [20].

Furthermore, the study interventions emphasize the importance of recording in-hospital falls and their circumstances, especially time. Therefore, it represents a change in health policy. In previous studies [6], a low incidence of falls has been detected in the hospitals of Andalusia, being less than 1 %, although 65 year olds are the population that suffers the most from these types of events, which is contradictory. Contradiction contrasted with other studies [24], where healthcare professionals showed that there is an underestimation of hospital falls. On the other hand, the previous studies that support the present project [20] found high incidences as a result of an appropriate registry of these events.

Nurses routinely need 24 h per day to care for patients, in many different settings and environments. The impact on physical and psychological well-being of shift work management and lengths of shifts have been largely studied [36, 37]. The findings emerging from these investigations are that anomalies of the circadian rhythm summed with the characteristics of shift workers may have a direct influence on the health of nurses [38]. The outcome to be analysed in the proposed study relate chronotype, sleep quality and health status of the nurse with the quality of clinical practice and ultimately patient safety.

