### Limitations

In the quantitative phases, the non-visualization of the fall may suppose an uncertain record of the event and its circumstances. Furthermore, both the record of falls and the section related to the state of health of the professionals are circumscribed to the idiosyncrasy of healthcare professionals. Limitations that are also present in the retrospective phase. A clinical trial could have more generalizability of the results and less bias. However, it should be noted that the interventions are established based on temporal patterns of incident events and relative risk factors for falls and related injuries in the participating hospitals. Therefore, with the intention of improving patient safety, the intervention is tailored to the casuistry of each centre.

The data obtained in the qualitative phase are subjective to perceptions of healthcare professionals. They cannot always express their opinions [40].

An information sheet on the study will be delivered to both the patient and the participating professionals, for which they will need to sign the informed consent.

For the retrospective study, the data will be delivered to the Principal Investigator anonymized.

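### Step 1 falls both select the temporal patterns the programme targets and serve as their 'pre' side, so patterns followed from Step 1 can appear to flatten with no programme effect

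*Protocol article*

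**What the plan says.** Four statements in the protocol article bear on this.

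- **Step 1 informs the programme.** Data collection: Procedure says "After obtaining and analysing the falls that occurred during the first 18 months of the study, time-adjusted preventive measures will be carried out". Study variables (Step 2) describes the programme as "adjusted to the identification of temporal patterns of falls and relative risk factors of falls", and Limitations says that "the intervention is tailored to the casuistry of each centre".
- **Step 1 is also the baseline.** Secondary aim (i) is "to identify temporal patterns in the incidence of hospital falls and intrinsic and external risks factors, pre- and post-intervention". Aim (ii) is "to establish differences in temporal patterns according to the hospital setting (teaching or non-teaching) and the different types of wards", again before and after. The Phase 2 institutional records come from the same hospitals and the same months (Participants and setting), so they give no independent baseline.
- **Pattern analysis.** Data analysis describes simple and multi-component Cosinor fits with an F-test. It then lists MESOR, amplitude, peak and valley, introduced with "The descriptive parameters of the statistically significant temporal patterns are". No joint model of the two steps is described.
- **Main outcome.** "The main dependent variable will be the number of hospital falls".

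The Discussion adds the intended use: "Obtaining temporal patterns in hospital falls allows establishing high-risk periods during the day".

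**The concern.** A pattern found in Step 1 is found partly because it is real and partly because chance made it look large in those months. When the programme is aimed at such patterns, interest afterwards falls naturally on whether they have shrunk. The Step 1 value has been selected for being high and the post value has not, so the post value is lower on average with no programme effect. The shorter post period adds to this for significance: fewer falls give less power, so a real and unchanged rhythm is more easily lost than gained.

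At stake is the interpretation of aims (i) and (ii). A targeted peak that shrinks, or a rhythm that is significant before and not after, is what a reader would take as evidence that time-based prevention works. The risk is greatest in small series, and tailoring by centre and splitting by ward type both create small series.

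**Working it through.** The article gives no fall counts, amplitudes or expected flattening, so there is no stated figure to reproduce. The check simulates a programme that does nothing.

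**Inputs from the article.** Step 1 is 18 months. The post period, July 2019 to September 2020, is 15 months, so expected post falls = Step 1 falls × 15/18 (200 gives 167). The general significance level is 0.05 two-sided; the Cosinor paragraph prints 0.5.

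**Assumed.** Step 1 falls per analysed series; true 24-hour amplitude; the same hourly rates in both steps.

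**Method.** Hourly Poisson counts y in 24 bins, with a single 24-hour Cosinor y = M + b·cos(2πt/24) + g·sin(2πt/24). Relative amplitude = 100·√(b² + g²)/M. F = (SS_model/2)/(SS_residual/21). There were 50,000 pairs of series per setting.

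**Result 1: follow the patterns significant in Step 1 (p < 0.05) into the post period.**

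| Step 1 falls | True amplitude | Step 1 mean | Post mean | Non-significant post |
|---|---|---|---|---|
| 200 | 0% | 26.5% | 13.8% | 95% |
| 200 | 20% | 31.4% | 23.3% | 69% |
| 200 | 25% | 33.5% | 27.7% | 53% |
| 1000 | 25% | 25.4% | 25.5% | 1% |

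These amplitudes are half the peak-to-valley distance. The article defines amplitude as peak to valley, so its % AMP is twice as large, with ratios unchanged. On that scale the first row is 2 × 26.5 = 53.0 to 2 × 13.8 = 27.6, and the second is 2 × 31.4 = 62.8 to 2 × 23.3 = 46.6. In both rows the mean moves from the article's high band (above 50) to its moderate band (26–50) with no effect.

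**Result 2: refit every series in both steps, no selection.** At 200 falls the mean goes from 12.6% to 13.7% (no rhythm) and from 22.7% to 23.2% (true 20%). There is no flattening; the slight rise reflects the noisier, shorter post period.

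**Result 3: apply the significance filter separately in each step.** At 200 falls, mean amplitude among patterns significant in their own step goes from 26.5% to 29.0% (no rhythm) and from 31.4% to 33.7% (true 20%), so it does not fall. Loss of significance is still lopsided when a rhythm exists: at a true 20%, 25% of series lose it and 20% gain it, purely because the post period is shorter.

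**Result 4: post/pre rate ratio in the 4-hour window that was highest in Step 1** (a separate run, 40,000 pairs per setting).

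| Step 1 falls | No rhythm | True 25% | True 50% |
|---|---|---|---|
| 50 | 0.62 | 0.67 | 0.73 |
| 100 | 0.70 | 0.76 | 0.81 |
| 300 | 0.81 | 0.87 | 0.90 |
| 1000 | 0.88 | 0.94 | 0.95 |
| 3000 | 0.93 | 0.97 | 0.98 |

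**Result 5: all 24 hours.** The post/pre rate ratio for total falls is 1.00 in every setting.

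**Result 6: the proposed comparison.** With N₁ and N₂ the falls in each step, W = [(b₁/M₁ − b₂/M₂)² + (g₁/M₁ − g₂/M₂)²]/(2/N₁ + 2/N₂), referred to χ² on 2 df. At 200 falls, applied to every series, it is falsely positive in about 5% at each amplitude. Applied only to series significant in Step 1, it is falsely positive in 24% with no rhythm and 7% at a true 20%. The protection therefore comes from including all series as well as from the joint model.

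**The case against.** The strongest objection is that the article does not plan the comparison that creates the bias. The significance wording in Data analysis covers Cosinor results in general and is not confined to Step 1. Applied to both steps it produces no drop in amplitude (Result 3), and neither does an unselected refit (Result 2). No section plans a contrast at hours chosen from Step 1; the Discussion sentence on high-risk periods is not an analysis. The method of comparing pre and post patterns could be set out in a fuller document. Several measures, including footwear, the medication poster, and attention at meal and transfer times, are already listed, and a morning peak has prior support in the Background, so not every target comes from Step 1 noise. At the printed threshold of 0.5 the shrinkage is also milder: at 200 falls, 24.7% to 23.2% for a true 20%.

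Most of this stands. A reader might infer that peaks must flatten after the programme; the documents and the simulation do not support that. What the objection leaves in place is that the text commits Step 1 to both roles, aims the programme at what Step 1 shows, and describes no comparison that would guard against following only those patterns. The 0.5 threshold also does not help where there is no rhythm: half of pure-noise series qualify, and their mean amplitude goes from 17.6% to 13.7% at 200 falls.

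**Conclusion.** The point holds in conditional form. The double use of Step 1 is in the text. If patterns or hours singled out there are followed into the post period, they can appear to weaken without any programme effect. In small series the artefact can be large: amplitude roughly halved when there is no rhythm, about a quarter lower at a true 20% with 200 falls (1 − 23.3/31.4 = 26%), and a 4-hour window 10% to 38% lower with 50 to 300 falls. With many falls and a strong rhythm it is small: no amplitude drop at 1000 falls and a true 25%, and 2% to 5% in the window at 1000 to 3000 falls and a true 50%. All these sizes rest on assumed counts and amplitudes.

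The point concerns secondary aims (i) and (ii) and any hour-specific reading of benefit. A reader might extend it to the main outcome, but choosing hours from Step 1 does not bias the number of falls over all hours.

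**What to change.** 1. For aims (i) and (ii), list the series in advance. Compare pre and post patterns for every one, whatever its Step 1 significance, in one model of both steps with a step-by-rhythm (period-by-harmonic) term.
2. State that a pattern significant before and not significant after will not be read as a programme effect.
3. Label any contrast at hours or patterns chosen from Step 1 as exploratory, and judge it against the drop expected when the same selection is repeated by simulation under no effect.

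Holding back part of Step 1 as a clean baseline is not recommended. With the programme established in May 2019, choosing on 2018 data would leave only January to April 2019. Those four months do not match the seasons of the post period, and the Background says that month affects falls.

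The cost is a little more analysis work, possibly outside the named Cosinor software. Data collection, the programme and the analysis of total falls are unchanged.

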### Design

A mixed-method research design will be carried out. Three different study designs will be used:

***Phase 1.*** Prospective longitudinal study in two steps:

A first step of 18 months, in which a first intervention of audits and seminars in healthcare professionals will be carried out, focused on an effective and efficient registry of hospital falls in older people. This first phase is crucial to identify temporal patterns of falls in relation to specific intrinsic and extrinsic risk factors among hospitalized older people, as well as the levels of fatigue/sleepiness, attention and cognitive functionality of the healthcare professionals who attend to an in-hospital fall.A second step of application of a multidimensional prevention programme for 15 months focused on organizational, educational and behavioural elements applied to admitted older people and healthcare professionals.

***Phase 2.*** Retrospective study of the fall records found in the institutional databases of the study centres in the period between January 2018 and September 2020. This period covers the first (January 2018–May 2019) and second phases (June 2019–September 2020) of the project, as previously indicated.

***Phase 3.*** Descriptive exploratory study with a qualitative approach, focus groups made up of healthcare professionals: doctors, nurses and nursing assistants who provide and have provided their professional services in the field of study, in the periods in which the longitudinal and retrospective studies have been carried out.

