### Participants and setting

***Phase 1.*** The study subjects will be all those patients over 65 years of age who suffer one/several fall(s) during their admission to the Reina Sofia University Hospital in Córdoba and in the three regional hospitals of the Province of Córdoba (Cabra, Montilla and Pozoblanco) from January 2018 to September 2020.

Specifically, for the study of the levels of fatigue/sleepiness, attention and cognitive functionality of the healthcare professionals, the reference nurses of the older person who has an in-hospital fall during the study period will also be included.

***Phase 2.*** Institutional records of falls occurring in patients over 65 years old. In order to contrast with the prospective design, the institutional records of the four hospitals will be collected during the same period (January 2018 to September 2020).

***Phase 3.*** Healthcare professionals (doctors, nurses and nursing assistants) will be interviewed.

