### Data collection: Procedure

***Phase 1***: The project will be explained to the institutional managers of the centres included in the study, who will appoint a coordinator to ensure proper development and will work in coordination with the research team. In these meetings, the process of recording falls will be disclosed, as well as the other variables.

Prior to data collection, meetings will be held with those responsible for the Clinical Management Units and special mention will be made of the areas that are expected to have a greater number of events (internal medicine, neurology, trauma, rehabilitation, …). Additionally, the dynamics of data collection will be explained.

On the other hand, being focused more on healthcare professionals (especially nurses) from the different study centres, several seminars will be held (first intervention), explaining how data collection should be done, as well as the definition of variables included in the record sheet. Such seminars will be proportional to the number of workers in the different centres included, being distributed over different days so that the number of workers receiving information is as large as possible. In addition, specific audits will also be carried out in each Clinical Management Unit.

During the first 18 months of study development, each time a fall occurs, in addition to recording the circumstances of the fall, it is necessary to obtain the informed consent of the patient to know their quality of life, general functional status, sleep pattern and chronotype. In healthcare professionals, informed consent must also be obtained to know the previous variables, as well as the values of fatigue/sleepiness, attention and cognitive functionality. In this sense, as it has been commented on in the inclusion/exclusion criteria, these variables will only be known in the healthcare professionals responsible for the older person, who have visualized and/or attended the fall event, even though the fall may be the result of a collective lack of attention from all the staff and not from a single person.

Once the prospective data collection period has started (January 2018), monthly individualized audits will be carried out in the different Clinical Management Units, aimed at managing correct data collection. Furthermore, these audits will allow obtaining a perspective of the fall event in relation to the number and related circumstances.

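### The pre/post boundary is dated inconsistently: June 2019 changes sides between two statements, and the programme is established in month 17 although it is to follow analysis of 18 months of falls

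*Protocol article*

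**What the plan says.** All statements are in the Protocol article.

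- **Design, Phase 1.** The pre-programme step is "A first step of 18 months, in which a first intervention of audits and seminars in healthcare professionals will be carried out". It is followed by "A second step of application of a multidimensional prevention programme for 15 months".
- **Participants and setting.** Phase 1 covers patients who fall "from January 2018 to September 2020". Phase 2 is to collect institutional records over the same period, so that they can be contrasted with the prospective data.
- **Design, Phase 2.** The dates are split as follows: "This period covers the first (January 2018–May 2019) and second phases (June 2019–September 2020) of the project". The sentence presents this split as one already given.
- **Data collection: Procedure.** Prospective collection starts in January 2018. On the order of events: "After obtaining and analysing the falls that occurred during the first 18 months of the study, time-adjusted preventive measures will be carried out". On the programme date: "The establishment of the programme of time-adjusted prevention measures will be carried out in May 2019 in the four centres". On the post period: "The post-intervention data collection will cover July 2019 to September 2020".

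No section describes a run-in, washout or excluded transition month. The main aim is the effect of the programme, and the main dependent variable is the number of hospital falls.

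**The concern.** The study has no concurrent control, so the calendar cut is the only thing that defines exposure. If the cut is not fixed, neither is the main comparison.

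Two things do not fit together. First, the Phase 1 durations and the dated split put June 2019 on opposite sides, so two analysts following the text could classify that month differently. Second, the programme is meant to be built on temporal patterns from 18 months of falls, but it is established before the 18th month has begun.

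Three consequences could follow:

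- Baseline months may already carry some of the intervention, which pulls the estimate towards no effect.
- Phase 1 and Phase 2 may be compared over different pre and post windows. Part of any difference between them would then come from the windows rather than from how completely falls were registered.
- It is unclear which months of data shaped the programme.

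**Working it through.** **Inputs.** Start January 2018 (Procedure); end September 2020 (Participants and setting); steps of 18 and 15 months (Design); post collection from July 2019 and establishment in May 2019 (Procedure); dated split at May/June 2019 (Design).

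**Month counts.** Inclusive months = (year2 − year1) × 12 + (month2 − month1) + 1.

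| Window | Calculation | Months |
|---|---|---|
| Jan 2018 to Sep 2020 | 24 + 8 + 1 | 33 |
| Jan 2018 to Jun 2019 | 12 + 5 + 1 | 18 |
| Jul 2019 to Sep 2020 | 12 + 2 + 1 | 15 |
| Jan 2018 to May 2019 | 12 + 4 + 1 | 17 |
| Jun 2019 to Sep 2020 | 12 + 3 + 1 | 16 |
| Jan 2018 to Apr 2019 | 12 + 3 + 1 | 16 |

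The plan's total reproduces: 18 + 15 = 33. Within that window, 18 + 15 is obtained only with a cut between June and July 2019, which agrees with the July start of post collection. The dated split gives 17 + 16 and does not reproduce 18 + 15.

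No sentence labels June 2019 as pre in Phase 1. That is inferred from counting 18 months from January 2018. Treating June as an unstated gap would leave 17 pre months, and treating May and June as a gap would leave 16. Neither matches the stated 18.

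**Sequence.** May 2019 is month 17, with 16 full months before it. The 18th month, June 2019, had not begun, so an analysis of 18 months of falls could not be complete at that point.

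**Dilution if measures were active in the baseline.** Let r be the true rate ratio and k the number of exposed months among the 18 baseline months, with a constant underlying rate and full effect from the first exposed day.

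Estimated reduction = 1 − r / [((18 − k) + k × r) / 18]

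- r = 0.70, k = 2: 1 − 0.70 × 18 / 17.4 = 27.6%
- r = 0.70, k = 1: 1 − 0.70 × 18 / 17.7 = 28.8%
- r = 0.60, k = 2: 1 − 0.60 × 18 / 17.2 = 37.2%

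The 30% and 40% reductions are assumptions; the document gives no expected effect size.

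**Unequal lengths.** If raw counts were compared with no programme effect and a constant rate, 15 against 18 months would show 1 − 15/18 = 16.7% fewer falls, and 16 against 17 would show 1 − 16/17 = 5.9% fewer. Rates per month or per bed-day remove this artefact, but they do not settle which side June belongs on.

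**The case against.** The strongest defence is that establishment may mean set-up. The Study variables section says the measures are to be agreed with hospital managers and written into the hospitals' official objectives. The Procedure section speaks of managers and the research team implementing the measures, with seminars, after giving the July start of post collection. On that reading, delivery could have begun in July and no baseline month would be exposed. This stands as a possibility, so exposure of the baseline is not shown. It does not remove the sequence problem, because a programme set in May could not rest on falls through June. Nor does it explain why the dated split puts June in the second phase.

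A second defence is that the dated split describes phases of the project and is not expressly an analysis window for Phase 2. That is fair. But it appears in the Phase 2 description and claims to repeat dates that the Phase 1 durations contradict.

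Third, the shift is small, runs against the programme, and would be smaller still with gradual uptake. That also stands: the dilution figures are worst cases under the assumed effect.

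A reader might infer that three rival boundaries are stated. The text supports two, one month apart: June/July from the durations and the July start, and May/June from the dated split, with which a May establishment is compatible. The May date adds a conflict of sequence, not a third boundary.

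**Conclusion.** The inconsistency is real and can be checked from the dates alone. Durations of 18 + 15 months with a July 2019 post start do not agree with phases dated as 17 + 16 months, and June 2019 changes sides between them. Establishment in month 17 also conflicts with a programme that is to follow analysis of 18 months of falls. Which date is right cannot be told from the document.

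The possible bias is modest and towards the null. A true 30% reduction would be estimated at 27.6% at worst with two exposed months, or 28.8% with one. This assumes a constant underlying rate, full effect from the first exposed day, and measures actually in use in May or June 2019.

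A reader might go further and conclude that the baseline is contaminated, or that a disagreement between Phase 1 and Phase 2 could not be interpreted. The document supports neither. It does not say when delivery began, and each fall is recorded with its day and time, so the prospective data can be re-cut to one boundary; dated institutional records can be treated in the same way. The point still needs correcting, because the cut defines the comparison on which the main aim rests.

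**What to change.** 1. Reconcile the Design and Data collection: Procedure sections on two separate dates: when the programme was established, and when delivery of the measures began.
2. Apply one set of pre and post windows to both Phase 1 and Phase 2.
3. End the pre period before delivery began. If delivery preceded July 2019, leave the months from delivery start to the end of June 2019 out of the main comparison as a transition, and add a sensitivity analysis that includes them. Post stays July 2019 to September 2020 (15 months). The pre period is then 18 months if delivery began in July 2019, 17 if at the start of June, and 16 if at the start of May.
4. Correct the stated 18-month length to match, and state which months fed the Cosinor analysis that shaped the programme.

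**Cost.** Text changes and no new data. At most two of 18 baseline months leave the main comparison (2/18, about 11% of baseline falls at a constant rate). If delivery began in July 2019, nothing is lost.
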